### 2. Objectives and Hypotheses

Primary Objective: To measure the proportion of uncomplicated *P. falciparum* malaria patients who have an adequate clinical and parasitological response following treatment with mefloquine- artesunate, piperaquine-DHA, or Malarone. It is important to note that the objective is to measure the efficacy of each individual regimen, rather than to compare the efficacies of each regimen, one to another.

Secondary Objective: To determine whether previously identified molecular markers of drug resistance, and in vitro drug resistance assays, predict clinical outcome for the three treatment regimens under study.

Primary Hypothesis: The upper bound of the 95% confidence interval for the proportion of ACPR in subjects treated with mefloquine-artesunate will be <0.9. The lower bound of the 95% confidence interval for the proportion of ACPR in subjects treated with piperaquine-DHA or Malarone will be >0.9.

Secondary Hypothesis: The odds ratio for treatment failure will be >2 in the following cases (a) patients treated with mefloquine artesunate whose Day 0 parasites have pfmdr1 copy number >1.5, (2) patients treated with Malarone whose Day 0 parasites have either *pfdhfr* S108N + N51I , or *pfcytb* Y268N. Mean IC50 values for treatment drugs will be statistically significantly higher in subjects who do not have ACPR than in those who do.

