### 2. Sample Size

The sample size is based entirely on the primary objective and primary hypotheses. Several approaches to calculating the sample size yield a sample size of ~100 subjects per group. For example, consider that we want to demonstrate that mefloquine-artesunate has an efficacy of less than 90%. If the observed efficacy is 80%, as observed in our recent trial in Kampot Province, then for a sample size of 100, the upper 95% confidence interval for the efficacy is 87%. Consider that we want to show that the efficacy of Malarone or piperaquine-DHA is greater than 90%. For a sample size of 100, if the observed efficacy of either regimen is ≥97.5%, as observed in a previous WHO study in Oddarmeanchey, then the lower 95% confidence interval will be at 91%. Similarly, in order to have a power of 90% to detect the difference between an efficacy of 95% in one regimen and 80% in another, a sample size of 100 is required.

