### 3. Data Analysis

Data will be recorded on standardized case report forms, entered into an Access database, and exported for analysis in STATA, SPSS, and Mathematica.

Therapeutic Efficacy. Drug efficacy will be calculated as the percent of subjects not requiring alternative therapy during the 42-day course of the test and reported with 95% confidence intervals. This will be the primary analysis and, as recommended by WHO will be conducted as a per protocol (rather than intent to treat) analysis. One disadvantage of this approach is that data from subjects who drop out or are lost to follow up during the follow-up evaluation period are not used. As a secondary, alternative approach we will calculate the failure rate using Kaplan-Meier survival analysis. The failure rate will be calculated as 1-Π(ri-di)/ri , where ri is the number of subjects without a recrudescence just before time ti, di is the number who had a recrudescence at time ti, and Π is the product of the fractions, (r-d)/r, at all points, i. The drawback to this analysis is that it makes the assumption that the risk of recrudescence in the patients lost to follow-up is the same as that in those not lost. This may not be a good assumption. Therefore, sensitivity analyses will be performed to determine the effect on the reported failure rate of the extreme assumptions that either all patients lost to follow-up had recrudescences, or that they all did not have them.

Predictors of treatment failure. Data will be analyzed using standard statistical packages such as Stata, SAS or SPSS. Subjects will be categorized based on therapeutic outcomes, presence of the various genetic markers and other demographic and parasite factors that are putative determinants of treatment failure, e.g. age, parasite density, parasite clearance time. Bivariate associations will be examined between these markers and the outcomes. Chi square or Fisher’s exact tests for two-tailed significance at p <0.05 will be used for univariate frequency comparisons. Test for association at each marker will be performed, for example, one SNP at a time. Since this analysis is only powered to generate hypotheses, no correction will be made for multiple hypothesis testing. Variables significant in any of these analyses will be fit into a logistic regression model to identify factors that were collectively predictive of treatment failure.

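### The secondary hypothesis sets marker odds ratios above 2, but the planned marker tests compare them with 1, so significance alone does not establish it (minor)

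*Protocol*

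**What the plan says.** Protocol A.2 (Objectives and Hypotheses), Secondary Hypothesis: "The odds ratio for treatment failure will be >2 in the following cases". The cases are pfmdr1 copy number above 1.5 in patients given mefloquine-artesunate, and either a pfdhfr double mutation or a pfcytb mutation in patients given Malarone. The remaining part, on IC50, is worded as a significance statement.

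Protocol B.3 (Data Analysis), predictors of treatment failure: chi-square or Fisher's exact "tests for two-tailed significance at p <0.05 will be used for univariate frequency comparisons". It adds: "Test for association at each marker will be performed, for example, one SNP at a time". It then states: "Variables significant in any of these analyses will be fit into a logistic regression model". On the status of the analysis it says: "Since this analysis is only powered to generate hypotheses, no correction will be made for multiple hypothesis testing".

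Protocol B.2 (Sample Size): "The sample size is based entirely on the primary objective and primary hypotheses". The calculations there "yield a sample size of ~100 subjects per group". No figure is given for the marker analysis.

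**The concern.** A hypothesis that an odds ratio exceeds 2 has OR ≤2 as its complement. A chi-square or Fisher test rejects OR = 1. Rejecting OR = 1 leaves any value between 1 and 2 open, so the planned test and the stated hypothesis answer different questions. The logistic regression that follows takes in variables already significant against OR = 1 and does not refer to 2 either.

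The primary hypotheses in the same section are tied to inference: each compares a 95% confidence bound with 0.9. The IC50 part is coherent as well. Only the odds-ratio part states a threshold that no planned procedure uses. What is at stake is the wording of the secondary conclusion, namely whether the report may say that a marker more than doubles the odds of failure or only that it is associated with failure.

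**Working it through.** **Inputs from the protocol**
- About 100 subjects per arm (B.2).
- Share of samples at the site with copy number above 1.5: 0.49 (B.1.b, Study Location). In an arm of 100 this gives 49 marker-positive and 51 marker-negative subjects.
- Mefloquine-artesunate efficacy 80% (B.2), so 20% failure.
- Two-tailed test at 0.05 (B.3).

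The true odds ratios below are assumptions; the protocol gives none beyond the threshold of 2.

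**Reproducing the plan's figure.** B.2 states 100 per arm for 90% power to separate 95% from 80%. With n = [1.96·√(2·0.875·0.125) + 1.2816·√(0.95·0.05 + 0.80·0.20)]² / 0.15², the result is (0.9167 + 0.5838)² / 0.0225 = 100.07, which rounds up to 101. Power at 100 is 0.8998. The stated figure reproduces. There is none to reproduce for the markers.

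**Step 1: what a significant table shows.** Take 20 failures split between 49 marker-positive and 51 marker-negative subjects. For 14 v 6:
- OR = (14 × 45) / (35 × 6) = 630 / 210 = 3.0.
- SE of log OR = √(1/14 + 1/35 + 1/6 + 1/45) = √0.2889 = 0.5375.
- 95% CI = exp(1.0986 ± 1.96 × 0.5375) = 1.05 to 8.60.

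| Failures, marker + v − | Fisher p | OR | 95% CI |
|---|---|---|---|
| 13 v 7 | 0.137 | 2.27 | 0.82 to 6.29 |
| 14 v 6 | 0.046 | 3.00 | 1.05 to 8.60 |
| 15 v 5 | 0.012 | 4.06 | 1.34 to 12.25 |
| 16 v 4 | 0.0024 | 5.70 | 1.75 to 18.59 |
| 17 v 3 | 0.0003 | 8.50 | 2.30 to 31.39 |

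Three successive significant splits (14, 15 and 16 positive) have intervals that include 2. The lower limit first exceeds 2 at 17 v 3. For 14 v 6 the chi-square p is 0.036 without continuity correction and 0.064 with it.

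**Step 2: how often each criterion is met.** For each true OR, solve p₁ = OR·p₀ / (1 − p₀ + OR·p₀) with (49p₁ + 51p₀)/100 = 0.20. At OR 2 this gives p₁ = 0.256 and p₀ = 0.147. Then sum the binomial probabilities Bin(a; 49, p₁) × Bin(c; 51, p₀) over all tables that meet the criterion. Significance is counted only in the direction OR >1. Chi-square is uncorrected. The interval is the Wald interval on the log OR, with 0.5 added to each cell if any cell is zero.

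| True OR | Fisher p <0.05 | Chi-square p <0.05 | Lower 95% limit >2 |
|---|---|---|---|
| 1 | 1.9% | 2.4% | 0.0% |
| 1.5 | 10.2% | 12.2% | 0.4% |
| 2 | 23.9% | 27.2% | 1.8% |
| 4 | 71.5% | 74.8% | 19.8% |
| 6 | 89.4% | 91.0% | 42.8% |

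The tests hold their level against their own null (row 1). At OR 2, where the hypothesis is just false, they are significant in about a quarter of trials; the confidence-limit criterion is met in 1.8%.

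**Sensitivity.** With 10% failure (assumed) and a true OR of 2, the rates are 14.6% (Fisher), 17.0% (chi-square) and 0.3% (lower limit >2).

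**The case against.** The strongest reply is that the protocol nowhere says p <0.05 will be taken as proof of OR >2. B.3 speaks of testing association, and the secondary objective asks only whether markers and in vitro assays predict outcome, which an association test does address. On that view, 24% to 27% at a true OR of 2 is the power to detect a real association and not an error rate. This stands. A reader might infer that the trial will announce OR >2 at about five times the nominal 5% error rate; that needs a decision rule the protocol does not contain.

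A second reply is that the threshold may refer to the point estimate. In this arm any Fisher-significant table with 20 failures already has an observed OR of at least 3.0, so significance would satisfy that reading. Significance combined with an observed OR above 2 also controls error against no association (1.9% by Fisher at true OR 1). This stands too, but that rule does not control error against an OR of 2 or less, and the protocol does not say which reading it means.

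Third, B.3 declares the analysis only hypothesis-generating, and the sample size does not rest on it. That limits the consequence but does not make a test of OR = 1 speak to OR >2.

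Finally, the absence of a stated confidence interval for the odds ratios carries no weight: such reporting is commonly left to a statistical analysis plan, and the planned logistic regression yields odds ratios in any case.

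**Conclusion.** The mismatch is real and lies within the protocol: A.2 sets a threshold of 2, and the test that B.3 fixes uses 1. A significant marker result would support association, but would not by itself establish that the odds of failure are more than doubled. It would be too strong to say that significance fails to support the hypothesis at all, given the observed ORs that significance requires in this arm.

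The figures rest on 100 subjects, 49% marker prevalence and 20% failure in the mefloquine-artesunate arm. They become false-positive rates only if significance is read as confirming OR >2. The Malarone arm has the same mismatch in wording, but the protocol gives no prevalence for its markers, so no size is put on it here. The primary analysis, the sample size and the IC50 hypothesis are unaffected. Severity is minor.

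**What to change.** Either of two changes closes the gap.

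1. In B.3, report each odds ratio named in A.2 within its own treatment arm with a 95% CI (exact or profile-likelihood where failures are few, as is likely with Malarone). Claim OR >2 only if the lower limit exceeds 2. If the lower limit exceeds 1 but not 2, claim association only.
2. Restate the A.2 hypothesis as OR >1, which matches the planned chi-square or Fisher test and leaves B.3 unchanged.

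Each takes a sentence or two and no new data. The cost of the first is a less favourable claim: in the mefloquine-artesunate arm the lower limit exceeds 2 in only about 20% of trials at a true OR of 4 and 43% at a true OR of 6. For 80% power on that criterion the arm would need about 517 or 243 subjects respectively (Wald approximation on the log OR, same prevalence and failure rate), against 100 planned. Since the sample size was not set for this question, the second change is the more practical if no claim about a doubling of the odds is intended.

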## B. EXPERIMENTAL METHODS

### 1. Experimental procedures and rationale

#### a. Justification for the use of human subjects, including children

The objective of the study is to measure the clinical effectiveness of commonly used anti-malarial drugs against *P. falciparum* malaria. It is possible to conduct in vitro drug resistance assays, however the clinical cure rate is not accurately predicted by the in vitro drug resistance assays, particularly in settings in which there is some degree of acquired immunity to malaria. Therefore, information about clinical cure rates needed to make decisions about anti-malarial drug policy can only be obtained from human studies. In areas where malaria transmission occurs adults may have partial clinical immunity to malaria. Even drug resistant malaria parasites may be cleared by treatment with drugs to which the parasite is resistant, because of the synergistic effect of partial immunity and partially effective drugs. Efficacy studies which exclude children may therefore overestimate efficacy and do not provide efficacy data for the population at greatest risk of death from malaria. It is therefore important to measure efficacy in a population which includes children.

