#### b. Study Location

The study will be conducted at the Trapeang Prasat Health Center in Oddarmeanchey Province, Cambodia. This site is in a rural, agricultural area about 8 hours by road from Phnom Penh. Falciparum malaria is common in the area around the health center. The health center participates in a current surveillance program to measure the prevalence of molecular markers of drug resistance in *P. falcparum*. In the first six months of surveillance, the health center enrolled 450 subjects over age 5. Of these, 433 (96%) had parasitemia > 1000 parasites/µl. The mean pfmdr1 copy number was 1.89 (95% CI 1.78, 2.00) and the proportion of samples with copy number >1.5 was 0.49. Although this prevalence of amplified *pfmdr1* genes is lower than at Chumkiri, the site at which we found an unexpectedly high failure rate for mefloquine-artesunate (10), it is elevated compared to sites in eastern Cambodia from which mefloquine resistance has not been reported. We expect, therefore, both that the number of eligible subjects will be sufficient and that there is a reasonable likelihood of finding mefloquine artesunate resistance in this site.

All laboratory analyses will be conducted at one of the collaborating Cambodian institutions, the National Malaria Center, or the Institute Pasteur de Cambodge. Confirmation of microscopic diagnosis of malaria will be performed at the National Malaria Center. RT-PCR based SNP and gene amplification assays for detection of molecular markers of drug resistance will be performed at Institute Pasteur or CNM; both these laboratories have experience in performing the RT-PCR assays. In vitro drug resistance assays will be performed at the Pasteur Institute.

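### The p<0.05 entry rule gives the pre-specified resistance markers an adjusted odds ratio only when they are already significant in the same data, so that estimate is often missing and, when present, selected to be large

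*Protocol*

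**What the plan says.** Section A.2 makes prediction of outcome by known resistance markers the secondary objective and states a directional hypothesis: "The odds ratio for treatment failure will be >2 in the following cases". The first case is "patients treated with mefloquine artesunate whose Day 0 parasites have pfmdr1 copy number >1.5"; the second concerns named pfdhfr and pfcytb mutations in the Malarone arm.

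Section B.3, under predictors of treatment failure, sets a two-step analysis. Chi-square or Fisher's "exact tests for two-tailed significance at p <0.05 will be used for univariate frequency comparisons", one marker at a time. Then: "Variables significant in any of these analyses will be fit into a logistic regression model". The candidates also include "other demographic and parasite factors that are putative determinants of treatment failure, e.g. age, parasite density, parasite clearance time". On its status the section says: "Since this analysis is only powered to generate hypotheses, no correction will be made for multiple hypothesis testing".

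Section B.1.a explains why immunity matters for cure: even resistant parasites may clear in partly immune adults "because of the synergistic effect of partial immunity and partially effective drugs".

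**The concern.** A screen on univariate significance suits a search among many SNPs. It suits less well a marker and effect size named in advance. Under the rule as written, a named marker that misses p<0.05 gets no adjusted estimate. One that passes gets an estimate conditional on having looked strong. Age and parasite density, which the protocol itself suspects of affecting cure, are left out whenever their own tests miss 0.05, which amounts to fixing their coefficients at zero.

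At stake is the adjusted answer to the secondary objective: whether it exists, and whether its size can be read at face value.

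**Working it through.** **Inputs.** From section B.2: about 100 subjects per arm; 80% efficacy for mefloquine-artesunate, hence 20 failures; at least 97.5% for the other two regimens, hence at most 2 to 3 failures in each. From section B.1.b: "the proportion of samples with copy number >1.5 was 0.49". From A.2: odds ratio 2 as the edge of the hypothesised range. From B.3: two-sided 0.05. Assumed, because the protocol does not give them: the odds ratios for age and density, and the age cut (40% of subjects below it unless stated otherwise).

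**The protocol's own figures.** For 80/100 the upper 95% limit is 86.7% (Wilson) or 87.3% (exact), against 87% stated. For 95% versus 80% at 90% power the usual formula gives 101 per group, against 100 stated. Both reproduce. B.2 bases the sample size on the primary objective, and no power is stated for the predictor analysis.

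**Power of the screen at odds ratio 2.**
- Solve 0.51·p0 + 0.49·p1 = 0.20 with odds ratio 2: p0 = 0.147, p1 = 0.256, difference 0.109.
- Null standard error: √(0.20 × 0.80 × (1/49 + 1/51)) = 0.080. Alternative standard error: √(0.256 × 0.744/49 + 0.147 × 0.853/51) = 0.080.
- z = (0.109 − 1.96 × 0.080)/0.080 ≈ −0.60, so power is about 27%.
- Simulated 2×2 tables give 28% (chi-square) and 23% (Fisher). Pooling all arms (300 subjects, 25 failures) gives 37% and 32%.

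**Why a retained estimate is large.** Take 49 marker-positive and 51 marker-negative subjects with 20 failures.
- 13 versus 7 failures: odds ratio (13 × 44)/(36 × 7) = 2.27, chi-square p = 0.11. Not admitted.
- 14 versus 6 failures: odds ratio (14 × 45)/(35 × 6) = 3.0, chi-square p = 0.036, Fisher p = 0.046. Admitted.

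With this split, no observed odds ratio between 1 and 3 can enter the model, although the hypothesis begins at 2.

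**The two-step rule simulated** (arm of 100, 20% failure, marker prevalence 0.49, age independent of marker, age odds ratio 2, chi-square screen):

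| True marker OR | Marker enters | Median OR when it enters | Median OR, marker + age always fitted |
|---|---|---|---|
| 2 | 25–27% | 3.7 | 2.0–2.1 |
| 3 | about 55% | 4.3 | 3.1 |
| 4 | about 73% | 5.0 | 4.2 |

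**What causes the inflation.** At a true odds ratio of 2, the unadjusted marker odds ratio over all trials has median 2.0. The always-fitted marker + age model, restricted to its own significant results, has median 3.8 to 3.9. So the cause is selection on significance; omitting an independent age effect does not produce it.

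**Omission of age or density.** At an assumed odds ratio of 2, age is dropped in about 72% of trials. At an assumed odds ratio of 3 it is dropped in about 40%, rising to 55–57% for age and density with Fisher's test, 30% in the younger age group and half with high density.

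**False positives.** With a null marker, the full two-step procedure rejects in about 3–4% of trials.

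**The case against.** The strongest reply is that B.3 already calls this analysis hypothesis-generating and tests every marker bivariately, while A.2 never says that its odds ratio is adjusted. The secondary hypothesis therefore gets a test whether or not the marker enters the model. That stands: what is missing is an adjusted estimate, not any answer. But the hypothesis-generating remark is offered as the reason for not correcting for multiplicity. It does not justify selecting pre-named markers on significance, and low power makes that selection worse.

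Four stronger readings are tempting, and the documents do not support them.
- A reader might infer that dropping age or density is what inflates the marker's odds ratio. With age and marker independent it is not, and no section links age to pfmdr1 copy number. Confounding is possible but would have to be assumed.
- A reader might infer that the marker is nearly always lost. That depends on the true effect: A.2 predicts an odds ratio above 2, and at 3 the marker enters in more than half of trials.
- A reader might infer that the protocol takes a non-significant test as proof of no effect. It does not say so; the exclusion only has that consequence inside the model.
- A reader might infer an excess of false positives. There is none.

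It is also fair to object that a three-predictor model cannot be asked of every arm. With 2 to 3 failures expected on Malarone it would carry no information.

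**Conclusion.** The point holds as a limited, inexpensive improvement to a secondary analysis. The entry rule is explicit and sits badly with the markers and effect size fixed in A.2. At the protocol's own failure rate, prevalence and threshold effect, the adjusted odds ratio for pfmdr1 copy number would be available in about a quarter of trials, with a median near 3.7 for a true value of 2. At a true odds ratio of 3 it would be available in about 55%, and the exaggeration is smaller.

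The marker result rests on 20 failures in 100 subjects and on analysis within the arm. The statement on age and density rests on assumed effects and cuts, and supports only that either can be omitted through low power. The primary efficacy estimates and the sample size are untouched.

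**What to change.** Amend the last step of section B.3 as follows.
- For each marker named in A.2, report the odds ratio with its 95% CI whatever the univariate p-value.
- In the mefloquine-artesunate arm, fit one logistic model with pfmdr1 copy number >1.5, age and log10 Day 0 parasite density, regardless of p, by Firth's penalised likelihood.
- In the Malarone arm, report only the unadjusted exact or Firth odds ratio with its CI.
- Keep p<0.05 screening for the other SNPs, labelled exploratory.

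The unselected estimate must also be the one that is presented. If only significant results are highlighted, the same inflation returns under the new model.

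The cost is a few sentences. Age and Day 0 parasite counts are already on the case report form. The small downside is 20/3, or about 6 to 7, failures per parameter in the mefloquine-artesunate model, which the penalised fit is meant to handle; the always-fitted marker + age model above, without penalisation, had a median close to the true value.
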